## Abstract

**Background:**

The incidence of metachronous contralateral inguinal hernia (MCIH) is high in infants with an inguinal hernia (5–30%), with the highest risk in infants aged 6 months or younger. MCIH is associated with the risk of incarceration and necessitates a second operation. This might be avoided by contralateral exploration during primary surgery. However, contralateral exploration may be unnecessary, leads to additional operating time and costs and may result in additional complications of surgery and anaesthesia. Thus, there is no consensus whether contralateral exploration should be performed routinely.

**Methods:**

The Hernia-Exploration-oR-Not-In-Infants-Analysis (HERNIIA) study is a multicentre randomised controlled trial with an economic evaluation alongside to study the (cost-)effectiveness of contralateral exploration during unilateral hernia repair. Infants aged 6 months or younger who need to undergo primary unilateral hernia repair will be randomised to contralateral exploration or no contralateral exploration (*n* = 378 patients). Primary endpoint is the proportion of infants that need to undergo a second operation related to inguinal hernia within 1 year after primary repair. Secondary endpoints include (a) total duration of operation(s) (including anaesthesia time) and hospital admission(s); (b) complications of anaesthesia and surgery; and (c) participants’ health-related quality of life and distress and anxiety of their families, all assessed within 1 year after primary hernia repair. Statistical testing will be performed two-sided with *α* = .05 and according to the intention-to-treat principle. Logistic regression analysis will be performed adjusted for centre and possible confounders. The economic evaluation will be performed from a societal perspective and all relevant costs will be measured, valued and analysed.

**Discussion:**

This study evaluates the effectiveness and cost-effectiveness of contralateral surgical exploration during unilateral inguinal hernia repair in children younger than 6 months with a unilateral inguinal hernia.

**Trial registration:**

ClinicalTrials.govNCT03623893. Registered on August 9, 2018

Netherlands Trial Register NL7194. Registered on July 24, 2018

Central Committee on Research Involving Human Subjects (CCMO) NL59817.029.18. Registered on July 3, 2018

## Administrative information

The order of the items has been modified to group similar items (see http://www.equator-network.org/reporting-guidelines/spirit-2013-statement-defining-standard-protocol-items-for-clinical-trials/).

## Introduction

### Background and rationale {6a}

Inguinal hernia is the most common paediatric surgical disorder with an incidence of 0.8–5% during childhood age and up to 30% in infants born preterm [1, 2]. The processus vaginalis normally obliterates spontaneously before or shortly after birth. If it remains patent, then fluid, fat or intestines can move into the open inguinal canal and present as a clinically visible hernia. Surgical repair (i.e. closing the patent processus vaginalis (PPV)) is recommended shortly after diagnosis because of the risk of incarceration, which is reported to be 3–30% in the first 6 months of life and even higher if the infant was born preterm [3].

Eighty percent of children with inguinal hernia present with a unilateral hernia, of which 10–15% develops a metachronous contralateral inguinal hernia (MCIH) [4]. Infants younger than 6 months old have the highest risk of developing MCIH [3, 5–7]: the overall risk for MCIH in 49,568 children undergoing unilateral hernia repair from 61 studies was 5.8%. However, in infants who were younger than 6 months (*n* = 1470), the risk for MCIH development was substantially higher at 12.4% [4]. Because an MCIH almost invariably necessitates a second operation and increases the child’s potentially harmful exposure to a second anaesthesia session, preventive strategies (e.g. contralateral exploration) have been proposed since the 1950s. Exploration of the asymptomatic, contralateral groin during unilateral hernia repair enables simultaneous inspection of the contralateral processus vaginalis and subsequent closing of a PPV, if present. Consequently, repair of an open processus vaginalis during contralateral exploration can prevent potential MCIH [8]. Especially since the predictive value of prognostic factors [9] and diagnostic modalities (e.g. preoperative ultrasonography) for development of MCIH are insufficient to specifically target children that will develop MCIH [10], routine contralateral exploration might therefore be beneficial. In infants less than 6 months old, nine contralateral explorations will be required to prevent one MCIH [4, 11].

Surgeons may prefer performing contralateral exploration because of high MCIH incidence, high incarceration rate and repeated anaesthesia, carrying risk for near critical incidents (apnoea risk up to 12%) [12]. The US Food and Drug Administration (FDA) recently released an official warning regarding the potentially harmful impact of repeated general anaesthesia on the child’s brain [13]. Indeed, previous studies have shown that multiple exposures to general anaesthesia before 3 years of age is associated with neurocognitive and developmental problems (e.g. learning disabilities) [14–17]. More recent research has shown that the potential impact of a single session of general anaesthesia for hernia repair on functional brain development is not detectable [18, 19]. Yet, the effect of repeated anaesthesia on brain development remains unclear [13, 18]. These findings highlight the importance of preventing repeated surgery and anaesthesia. Contralateral exploration may help to reduce the frequency and total length of anaesthesia in children that develop MCIH after unilateral hernia repair.

Nonetheless, contralateral exploration also carries additional risks of operative complications: wound infection occurs in 0.6–1.2% of the children, hematoma in 0.1%, testicular atrophy in 0–0.3% and ipsilateral recurrence in 0.4–1.2% [20, 21]. In preterm babies, these risks are even higher: the recurrence rate varies from 2 to 8.6% and the risk of testicular atrophy, which may be accompanied by loss of function, ranges from 2 to 30% [3, 5]. If both testes are affected, boys may become infertile. As not all PPVs necessarily become hernias, contralateral exploration and its additional risks will be unnecessary in some children [22]. Consequently, the debate continues whether or not to perform contralateral inguinal exploration in infants with inguinal hernia [4, 9, 20]. Cost-effectiveness of both strategies in children has never been assessed.

### Objectives {7}

We hypothesise that open contralateral exploration with subsequent contralateral hernia repair prevents second surgery and repeated exposure to anaesthesia and that the risk of surgical complications equals the complication rate of symptomatic hernia repair. Prevention of MCIH and avoiding second anaesthesia and surgery together with its potential risks and complications possibly outweighs the potential burden of contralateral exploration. Complications following negative contralateral exploration will be even less.

### Study objectives

The Hernia Exploration oR Not In Infants Analysis (HERNIIA) trial aims to study the effectiveness and cost-effectiveness of contralateral inguinal exploration in infants aged 6 months or younger with a unilateral inguinal hernia compared with unilateral repair only.

### Trial design {8}

A prospective, parallel group, multicentre randomised controlled trial (RCT) will be conducted including infants aged less than 6 months who present with unilateral inguinal hernia. The SPIRIT 2013 Statement (Standard Protocol Items: Recommendations for Interventional Trials) and SPIRIT 2013 Explanation and Elaboration paper for Randomised Trials [23] were used for complete and transparent reporting of the trial protocol.

## Methods: participants, interventions and outcomes

### Study setting {9}

Five paediatric surgical centres in The Netherlands (Amsterdam UMC: Emma Children’s Hospital AMC and VU medical centre; University Medical Centre Groningen; Maastricht University Medical Centre; Erasmus MC - Sophia Children’s Hospital Rotterdam), Juliana Children’s Hospital Den Haag and Maxima Medical Centre Veldhoven participate in this trial. Inguinal hernia repair is performed in clinical or day care setting depending on the postnatal age and gestational age of the infant.

### Eligibility criteria {10}

#### Inclusion criteria

Infants aged younger than 6 months at first presentation with a primary unilateral inguinal hernia undergoing open hernia repair are considered eligible for inclusion.

#### Exclusion criteria

Infants with (1) incarcerated inguinal hernia requiring urgent surgery, (2) a ventricular-peritoneal drain and (3) non-descended testis will be excluded.

### Who will take informed consent? {26a}

The surgeon explains the study to the parents/caretakers, hands over the information letter and informed consent form, and asks permission to hand over their contact details to the research team. A member of the research team will contact the parents/caretakers to provide more details and answer questions if necessary. As most infants are operated within 3–4 weeks after the outpatient clinic visit, there will be enough time for parents/caretakers to discuss the study and ask any questions before consent needs to be given. At each centre, all (fellow) surgeons who will be involved in this clinical trial will receive training in order to provide information to the parents/caretakers according to the standard operating procedure (SOP) and Good Clinical Practice (GCP) guidelines.

### Additional consent provisions for collection and use of participant data and biological specimens {26b}

Not applicable, as these will not be collected.

## Interventions

### Intervention description {11a}

Open inguinal hernia repair in infants younger than 6 months old is performed by experienced (fellow) paediatric surgeons. It is the most commonly performed operation in children and no substantial variations in operation technique exist. Therefore, no additional training is necessary for the purpose of this study.

#### Intervention group: unilateral hernia repair with contralateral exploration

Surgical inguinal hernia repair is done similarly in all patients. An incision is made in the groin. The hernia sac is identified, divided from the vas deferens and testicular vessels (in boys) and cleaned to the level of the internal inguinal ring. It is twisted on itself and ligated at the level of the internal inguinal ring. The skin is closed. Duration of unilateral inguinal hernia repair is approximately 60 min (including anaesthesia time). Exploration of the contralateral side and potential contralateral hernia repair will increase anaesthesia time by approximately 15 min.

Contralateral exploration will be used to identify a PPV or hernia on the other side than the side on which the child has to be operated on. If during contralateral exploration, a hernia or PPV is present, contralateral repair will be performed. This will be exactly the same procedure as the inguinal hernia repair on the symptomatic side. If a hernia or PPV is absent during contralateral exploration, the skin will be closed. There is no need for extension of postoperative hospital admission or addition of other interventions.

### Explanation for the choice of comparators {6b}

#### Control group: unilateral hernia repair without contralateral exploration

In participants who are allocated to the control group, only unilateral hernia repair (without contralateral exploration) will be performed.

### Criteria for discontinuing or modifying allocated interventions {11b}

Parents can decide to leave the study at any time for any reason, and without any consequences. The investigator can also decide to withdraw a subject from the study for urgent medical reasons. Participants will not be replaced after withdrawal. Protocol violations (e.g. if study participants do not receive the treatment strategy which is allocated by randomisation) will be recorded.

### Strategies to improve adherence to interventions {11c}

Not applicable, since the intervention in both groups comprises surgical treatment.

### Relevant concomitant care permitted or prohibited during the trial {11d}

Concomitant surgery such as orchidopexy is permitted during the trial, but will be registered.

### Provisions for post-trial care {30}

The sponsor has an insurance, which is in accordance with the legal requirements in the Netherlands (Article 7 WMO (Medical Research Involving Human Subjects Act)). This insurance (Onderlinge Waarborgmaatschappij Centramed B.A. [name]) provides cover for damage to research subjects through injury or death caused by the study. The insurance applies to the damage that becomes apparent during the study or within 4 years after the end of the study. Subjects who participate in the study will receive information about this insurance.

## Outcomes {12}

### Primary outcome measure

Primary outcome is the proportion of reoperations within 1 year after primary hernia repair. This will be calculated using the number of infants that undergo a second operation related to inguinal hernia repair within 1 year following primary repair, as a fraction of the total number of infants in that group. All participants are seen by a (fellow) paediatric surgeon at the outpatient clinic or via a digital consult 1 year after primary hernia repair. The latter is done to score development of contralateral hernia, testicular atrophy and/or recurrence.

### Secondary outcome measures

#### Total duration of operation(s) including anaesthesia time and hospital admission(s)

Duration of operation(s) including anaesthesia time will be calculated in minutes from start of anaesthesia induction until end of anaesthesia. Length of hospital stay will be calculated as the number of days a patient is admitted to the hospital. This will be recorded by the (fellow) paediatric surgeon during each separate hospital admission/visit for inguinal hernia (repair).

#### Complications of anaesthesia and surgery

Complications related to inguinal hernia within 1 year after primary repair are as follows: wound infection, hematoma, hydrocele, testicular atrophy, apnoea or inguinal hernia recurrence. Apnoea, wound infection, hematoma and hydrocele will be assessed during hospital admission via monitoring (if applicable) and by the (fellow) paediatric surgeon. After hospital discharge, these complications will be assessed through a phone call performed by one of the investigators 4 weeks following surgery. Testicular atrophy and inguinal hernia recurrence will be assessed at the outpatient clinic 1 year following surgery. If there is partial or complete testicular atrophy of one testis (i.e. one of the testes is smaller compared to the other at follow-up), additional ultrasonography of both testes will be performed. Complications are defined as:
Testicular atrophy: No palpable testicular tissue in scrotum (=complete testicular atrophy) or testis documented to be smaller at follow-up than at time of inguinal hernia repair (=partial testicular atrophy) at operated side(s).Wound infection/surgical site infection: Infection occurring within 30 days of surgery; infection involving only the skin and subcutaneous tissue; at least one of the following: (a) purulent discharge from a superficial infection or (b) organisms isolated from aseptically obtained wound culture; and at least one of the following signs of infection: (a) pain or tenderness, (b) localised swelling and (c) redness or hyperthermia [24].Apnoea: Apnoea of infancy is defined as “an unexplained episode of cessation of breathing for 20 seconds or longer, or a shorter respiratory pause associated with bradycardia, cyanosis, pallor, and/or marked hypotonia requiring intervention”. Types of interventions recorded will include stimulation, assisted ventilation, continuous positive airway pressure (CPAP), endo-tracheal intubation and administration of methylxanthine [25].Recurrence: the hernia returns at the previously operated side and a reoperation on the same side is warranted.

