### Post intervention assessment

Primary and secondary outcomes will be assessed during hospital admission, 4 weeks after primary hernia repair and 1 year after primary hernia repair. If patients develop MCIH within 1 year after primary inguinal hernia repair, baseline and outcome assessments will also be performed during and 4 weeks after MCIH repair.

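### Hydrocele is defined as a complication within 1 year, but the outcome-specific text schedules it only to 4 weeks and conflicts with the general assessment schedule

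*Protocol article*

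**What the plan says.** The window is set in the Complications of anaesthesia and surgery section: "Complications related to inguinal hernia within 1 year after primary repair are as follows: wound infection, hematoma, hydrocele, testicular atrophy, apnoea or inguinal hernia recurrence". The Abstract also places all secondary endpoints within 1 year of primary repair.

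The same section then assigns complications to time points. For the group that includes hydrocele: "Apnoea, wound infection, hematoma and hydrocele will be assessed during hospital admission via monitoring (if applicable) and by the (fellow) paediatric surgeon". Then: "After hospital discharge, these complications will be assessed through a phone call performed by one of the investigators 4 weeks following surgery". The 1-year visit is given to two other items: "Testicular atrophy and inguinal hernia recurrence will be assessed at the outpatient clinic 1 year following surgery".

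The Primary outcome measure section describes the 1-year contact: "All participants are seen by a (fellow) paediatric surgeon at the outpatient clinic or via a digital consult 1 year after primary hernia repair". Its purpose follows: "The latter is done to score development of contralateral hernia, testicular atrophy and/or recurrence". Hydrocele is not in that list.

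The Post intervention assessment section is broader: "Primary and secondary outcomes will be assessed during hospital admission, 4 weeks after primary hernia repair and 1 year after primary hernia repair". It does not break this down by outcome. It adds that infants who develop metachronous contralateral inguinal hernia (MCIH) are also assessed during and 4 weeks after that repair.

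Adverse event reporting and harms {22} ends the recording of adverse events at the first follow-up. Secondary study parameters plans an odds ratio with 95% CI for complications.

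**The concern.** The outcome has a 1-year label, while the text that says how it is measured stops at 4 weeks. Sites that follow the specific text will not score hydrocele at 1 year; sites that follow the general sentence may. The result would then be a mixture of 4-week and 1-year ascertainment, or a 4-week count under a 1-year name.

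It matters because the Objectives section hypothesises that the risk of surgical complications equals that of symptomatic hernia repair, and weighs prevented reoperations against the burden of exploration. Hydrocele is one of six listed complications in that comparison. An incomplete count understates its rate. Detection can also differ between arms, because reoperation for MCIH brings another admission and another 4-week assessment, and more of these are expected in the control arm.

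**Working it through.** **1. The text side by side**

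| Section | What it fixes | Hydrocele at 1 year? |
|---|---|---|
| Complications, opening sentence | 1-year window for all six complications | Implied by the window |
| Complications, assessment sentences | Admission, then telephone call at 4 weeks | No |
| Complications, 1-year sentence | Atrophy and recurrence | Not named |
| Primary outcome measure | Contralateral hernia, atrophy, recurrence | Not named |
| Post intervention assessment | All outcomes at admission, 4 weeks, 1 year | Yes in general terms, not itemised |
| Adverse event reporting {22} | Recording to first follow-up | No, if first follow-up is the 4-week contact (term not defined) |

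Wound infection has its own 30-day limit in the definitions, so a look at about 4 weeks roughly fits it. Hydrocele has no shorter window of its own, so the 1-year window governs.

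**2. Calendar time without a scheduled look**

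(52 − 4)/52 = 48/52 = 92%. This is a share of the year, not of events.

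**3. Extra looks by arm**

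Inputs from Sample size {14} and Sequence generation {16a}: 10% v 2.5% reoperated, total 378, 1:1 allocation, power 0.80, two-sided alpha 0.05. The stated total reproduces: the normal-approximation formula for two proportions gives 163 per arm without and 189 per arm with continuity correction, and 2 × 189 = 378.

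Expected infants with an additional admission and 4-week assessment:
- control: 189 × 0.10 = 18.9
- exploration: 189 × 0.025 = 4.7

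The difference is about 14 infants.

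**4. What incomplete capture would do (assumptions, not trial data)**

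The documents give no hydrocele rate or timing. Assume 1-year risks of 4% v 2% and a share f arising after week 4 and unrecorded. Captured cases per arm = 189 × risk × (1 − f):

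| f | Cases, 4% arm | Cases, 2% arm |
|---|---|---|
| 0 | 7.6 | 3.8 |
| 25% | 5.7 | 2.8 |
| 50% | 3.8 | 1.9 |
| 75% | 1.9 | 0.9 |

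At f = 50%, assumed risks of 2% v 1% give 1.9 v 0.9 captured cases, and 6% v 3% give 5.7 v 2.8.

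If loss is equal in both arms, the rate falls but the odds ratio hardly moves. For 4% v 2% it is (0.04/0.96)/(0.02/0.98) = 2.04 complete, and (0.02/0.98)/(0.01/0.99) = 2.02 at f = 50%. The cost is understated rates and fewer events.

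If the extra looks recover late cases, capture becomes unequal. Suppose late hydrocele is independent of reoperation and every reoperated infant's late hydrocele is found. The captured fraction is then 1 − f + 0.10f in control and 1 − f + 0.025f with exploration:
- f = 25%: 0.775 v 0.756, ratio 0.98
- f = 50%: 0.550 v 0.513, ratio 0.93
- f = 75%: 0.325 v 0.269, ratio 0.83

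Under these assumptions, a true risk ratio of 1 would appear as 0.98 to 0.83, in favour of exploration. If late hydrocele is more common in infants who also develop MCIH, the distortion could be larger; if the extra looks find only some cases, it is smaller.

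**The case against.** The strongest reply is that the Post intervention assessment section already schedules every secondary outcome at 1 year, so hydrocele is covered. That reading is possible. But the sentence is a summary, and the two places that itemise the 1-year contact both leave hydrocele out. What stands is that the sections conflict; one cannot conclude that hydrocele is certainly unscored at 1 year.

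Other routes could also capture late cases. The data collection section {18a} records hospital visits and complications without a 4-week limit, each hospital visit for inguinal hernia is recorded, and the cost questionnaire is repeated at 1 year. This stands too, but it is passive capture that depends on the infant coming to care.

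A reader might infer more than the documents support:
- **That late hydroceles will be missed, or that 92% of them are lost.** The 92% is calendar time, and it applies equally to wound infection, haematoma and apnoea.
- **That the Background shows hydrocele arising throughout the year.** The sentence containing "If it remains patent, then fluid, fat or intestines can move into the open inguinal canal" goes on to a visible hernia; it describes hernia formation and says nothing about when hydroceles appear.
- **That a telephone call cannot distinguish hydrocele from other swellings.** The documents offer nothing on this.
- **That a hydrocele in the control arm's unoperated groin counts as an endpoint event.** The outcome is headed as complications of anaesthesia and surgery, so this is open. Recording by side leaves both readings available.
- **That the 1-year contact guarantees a groin examination.** It may be a digital consult.

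Finally, this is a condensed article, and the full protocol or case report form may list hydrocele at 1 year. That would settle the practice, but the published sections would still disagree.

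**Conclusion.** The point holds as an inconsistency in the stated rules: a 1-year endpoint, outcome-specific assessment to 4 weeks, and a general sentence pointing the other way. Later hydroceles can be missed, and the control arm is expected to get more looks (about 19 v 5 infants, at the planning rates and 189 per arm). How many cases this concerns is unknown. The illustrations rest on assumed risks, an assumed late share and independence of hydrocele from reoperation. They suggest a small number of cases and, unless most hydroceles are late, a modest distortion between arms.

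The scope is one item of one secondary outcome. The primary outcome and the sample size of 378 do not depend on it. It should still be corrected, because otherwise a largely 4-week count could be reported as a 1-year complication odds ratio.

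**What to change.** Reconcile four sections: Primary outcome measure, Complications of anaesthesia and surgery, Post intervention assessment, and Adverse event reporting {22}.

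- Add hydrocele to the items scored at the existing 1-year contact, recorded by side (symptomatic, explored or unexplored groin). Mark it as parent-reported where the contact was digital.
- Keep the 4-week telephone report as a separately labelled early item.
- State which contact is the first follow-up that ends adverse-event recording.
- For infants already past their 1-year contact, or if the item is not added, label the endpoint as hydrocele up to 4 weeks after each operation and do not report it as a 1-year rate.

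The cost is one case report form item and a few lines of text. The drawback is incomplete 1-year data for infants already past that contact. At the recruitment count of 24 August 2021, 302 of the planned 416 were included, so 416 − 302 = 114 were still to be enrolled; infants operated on in the preceding year had not yet reached the 1-year contact either.

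### Complete testicular atrophy is defined by scrotal palpation alone, and the planned ultrasonography has no stated role in the final label, so a viable testis outside the scrotum would be scored as atrophy

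*Protocol article*

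**What the plan says.** All of this comes from the protocol article.

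- **Definition.** Under Complications of anaesthesia and surgery, complete atrophy is "No palpable testicular tissue in scrotum (=complete testicular atrophy"). Partial atrophy is a "testis documented to be smaller at follow-up than at time of inguinal hernia repair (=partial testicular atrophy) at operated side(s"). I read the restriction to operated sides as applying to both.
- **Ultrasonography.** The same section says: "If there is partial or complete testicular atrophy of one testis (i.e. one of the testes is smaller compared to the other at follow-up"), then "additional ultrasonography of both testes will be performed". It does not say what follows from the result.
- **Timing.** "Testicular atrophy and inguinal hernia recurrence will be assessed at the outpatient clinic 1 year following surgery". The Primary outcome measure section lets the 1-year contact take place "at the outpatient clinic or via a digital consult 1 year after primary hernia repair".
- **Listed complications.** Six are named. None concerns the position of the testis.
- **Entry and concomitant surgery.** Under Exclusion criteria, infants with "3) non-descended testis will be excluded". Item 11d adds: "Concomitant surgery such as orchidopexy is permitted during the trial, but will be registered".
- **Analysis.** Under Secondary study parameters, complications are summarised by an odds ratio with 95% confidence interval.

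**The concern.** Atrophy means loss of testicular tissue. The definition of its complete form uses location instead. A testis that was scrotal at entry but lies in the groin at 1 year satisfies the wording even if its volume is normal.

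Testicular atrophy is one of the main harms that the Background sets against exploration, with infertility mentioned if both testes are affected. The Objectives also hypothesise that exploration carries the same surgical complication risk as repair of a symptomatic hernia. A scoring rule that turns malposition into organ loss would distort the evidence on that hypothesis. It would do so unequally, because boys in the exploration arm have more operated groins in which the event can be scored.

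**Working it through.** **1. The rule applied to three boys, operated side, 1 year**

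| Finding | Label under the written definition | Correct? |
|---|---|---|
| No testis anywhere | Complete atrophy | Yes |
| Normal testis in the groin, none felt in the scrotum | Complete atrophy | No |
| Same boy, ultrasound shows a viable inguinal testis | Definition still met; the article does not say whether the label changes | Not settled |

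Non-descended testis is excluded at entry, so the second and third rows would mostly be events arising after entry. No other listed category would take them.

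**2. The plan's own figure**

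The documents state no rate or sample size for atrophy. The only stated calculation, 378 for the primary outcome (10% versus 2.5%, two-sided 0.05, power 0.80), reproduces as 189 per arm with a continuity correction. It serves here only as a denominator.

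**3. Illustration of size**

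Inputs from the documents: 189 per arm; about 10% of controls later operated on the other side; true atrophy 0–0.3% in children generally and 2–30% in preterm infants (Background).

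Assumptions, not in the documents: 80–90% boys; a = 0.5–2% of operated testes viable but outside the scrotum at 1 year; equal risk in every operated groin; the Background percentages applied per operated testis.

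- Boys per arm: 189 × 0.8 = 151 to 189 × 0.9 = 170.
- Operated testes, exploration: 2 × boys = 302–340. Control: 1.1 × boys = 166–187.
- Falsely scored events = operated testes × a. Exploration: 302 × 0.005 = 1.5 to 340 × 0.02 = 6.8. Control: 166 × 0.005 = 0.8 to 187 × 0.02 = 3.7.
- Excess in the exploration arm = 0.9 × boys × a: 0.9 × 151 × 0.005 = 0.7 to 0.9 × 170 × 0.02 = 3.1.
- True events at 0.3%: exploration 0.9–1.0, control 0.5–0.6.

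**4. Absolute rates and the planned odds ratio**

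Let q = true rate + a per groin, with independent groins. Exploration rate E = 1 − (1 − q)². Control rate C = 0.9q + 0.1E.

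| True rate | a | E | C | E − C | Odds ratio |
|---|---|---|---|---|---|
| 0.3% | 0 | 0.60% | 0.33% | 0.27 points | 1.82 |
| 0.3% | 0.5% | 1.59% | 0.88% | 0.71 points | 1.83 |
| 0.3% | 2% | 4.55% | 2.52% | 2.02 points | 1.84 |
| 2% | 0 | 3.96% | 2.20% | 1.76 points | 1.84 |
| 2% | 2% | 7.84% | 4.38% | 3.46 points | 1.86 |

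The absolute rates and their difference move. The odds ratio hardly does, because true and false events are assumed to scale with the same number of groins.

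**5. Upper bound**

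Two fully operated groins per exploration boy is the maximum. The Intervention description says that when neither hernia nor patent processus is found, the skin is simply closed, and the Objectives expect fewer complications after a negative exploration. If a negative exploration carried no malposition risk and a share f of explorations led to repair, the factor 0.9 would become (1 + f) − 1.1 = f − 0.1. The documents do not give f.

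**The case against.** The strongest reply is that silence is not prohibition. A reader might infer that the ultrasound cannot overrule the palpation label. No sentence says so. The article orders imaging of both testes in flagged boys, and the rule for using it may sit in the full protocol or the analysis plan, neither of which is shown. That stands. It does not remove the point, because the definition itself is stated, is complete as worded, and leaves the ultrasound out.

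Second, the sentence triggering the ultrasound explains atrophy as one testis being smaller than the other, which suggests that size is the intended concept, and a paediatric surgeon would probably recognise a normal inguinal testis. This makes literal misapplication less likely. But that explanation also differs from the definition of partial atrophy, which compares with size at repair, so it does not settle which rule governs.

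Third, item 11d might be taken to show that the trial expects displaced testes. It only permits and registers concomitant surgery. A malposition treated by orchidopexy would leave a record, but not as a listed complication.

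Fourth, one could divide the assumed malposition rate by 0.3% and conclude that false cases outnumber true ones by 1.7 to 6.7 times. That is only 0.5/0.3 to 2/0.3. At the preterm figures the same division gives 0.5/30 = 0.02 to 2/2 = 1.0, and the Background does not limit its figures to complete atrophy. The ratio should not be relied on.

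**Conclusion.** The point holds as a defect in a stated definition. Read literally, it scores a viable testis outside the scrotum on an operated side as complete atrophy, and no other listed complication takes the case. The bias would raise absolute atrophy rates in both arms, and more in the exploration arm.

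Its size cannot be derived from the documents. Under the stated assumptions the excess is at most about 0.7–3.1 events in the exploration arm. That is small in number, but not against roughly one true event in that arm at 0.3%; at preterm rates it matters proportionately less.

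The documents do not support the inference that the planned odds ratio would be seriously biased: it stays between 1.82 and 1.86 in the illustration. That stability depends on true and false events following the same per-groin pattern. The matter is confined to one component of a secondary safety outcome; the primary outcome and sample size are untouched.

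**What to change.** Change the outcome scoring only:

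1. Keep the absence of a palpable scrotal testis as the trigger for the ultrasonography already planned, not as the final label.
2. Classify complete atrophy only if no viable testis is found in scrotum or groin, with that ultrasound taken into account.
3. Record a testis outside the scrotum as a separate complication, per operated side.

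In the same edit, reconcile two neighbouring statements: the ultrasound trigger compares one testis with the other while partial atrophy compares with size at repair, and a digital 1-year consult does not allow the palpation on which the definition depends.

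Cost: one revised definition and one extra item on the case report form. No additional imaging is introduced beyond what is planned. The downside is that fewer events will be called atrophy, so the report should show both categories side by side.
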